## Abstract

The aim of this article is to present the research protocol for a study that will evaluate the feasibility of implementation of Health Arcade prototype multidomain intervention based on physical and cognitive training using gamification technologies at improving care for older people hospitalized with an acute illness. A total of 40 older people will be recruited in a tertiary public hospital at Pamplona, Spain. The intervention duration will be four to nine consecutive days. Additionally, the patients will receive encouragement for maintaining active during hospital stay and for reducing sedentary time. Primary implementation-related outcomes will be the adherence to treatment (i.e., number of games and days completed during the intervention period), reaction or response time, and number of success and failures in each game per day. Secondary implementation-related outcomes will be self-perceived grade of difficulty, satisfaction, enjoyment per game and session, and self-perceived difficulties in handling the prototype hardware. Other health-related outcomes will also be assessed such as functional capacity in activities of daily living, mood status, quality of life, handgrip strength, physical activity levels, and mobility. The current study will provide additional evidence to support the implementation of multidomain interventions designed to target older persons with an acute illness based on friendly technology. The proposed intervention will increase accessibility of in-clinical geriatrics services, improve function, promote recovery of the health, and reduce economic costs.

## 1. Introduction

The risk of loss of independence and the likelihood of developing new disabilities that increases with the ageing process is one of the major issues in developed countries. Such loss of functional independence, coupled with a gradual impairment of cognitive and physical abilities, is associated with a greater chance of institutionalization and mortality [1,2]. In this context, the World Health Organization (WHO) published the first “World Report on Ageing and Health” [3] in 2015. This framework emphasizes that care for older people must shift their main focus from disease to intrinsic capacity (i.e., physical function). This becomes particularly important when dealing with old people at risk of disability, also known as frail, to act on them early on.

One of the major events leading to disability in elderly adults is usually acute medical illness with its subsequent hospitalization. Hospitalization-acquired disability incidence usually varies between 5% and 60% [4,5]. Recent evidence has shed light on hospitalization-related iatrogenic disability in elderly people, which is frequently characterized by lengthy periods of bedrest. Previous studies have observed that the time that older adults spend outside of said bed, pacing or walking along available spaces in the hospitals ranges from 7 to 43 min per day, reaching 83 min per day when also counting the time they spend on their feet [6,7]. This phenomenon has been named “pyjama paralysis” [8]. The decrease in mobility during hospital-stays in conjunction with the reduction of functional and physiological reserves in elderly hospitalized patients may result in many adverse events. These adverse events include loss of autonomy regarding activities of daily living (ADLs), a higher incidence of falls, cognitive impairment, sarcopenia, reduced caloric intake and social isolation [9]. Thus, the hospitalization should turn out to be the turning point and the appropriate place for establishing interventions to prevent hospitalization-acquired disability [10].

In this scenario, serious games could present an innovative intervention. Serious games are defined as games in which the final goal is to promote a change in the user, not the training in and of itself. This change could range between the acquiring of new knowledge to changes in attitudes or even changes in cognitive, physical, and/or social abilities [11]. The design of these games is based exclusively on virtual and technological environments, comprising an important component of virtual reality simulation. Furthermore, recent evidence has proposed the term “gamification,” which is used to mention the gaming elements in non-gaming contexts with the aim of reaching a behaviour change in the user [11,12,13,14]. These interventions have been proven to be effective in different settings, such as children, teenagers, or young adults, mainly in education, commerce, and communication. [15,16,17,18,19,20]. However, current evidence suggests it is still necessary to redesign and adapt these technologies to the characteristics and preferences of old patients in order to achieve maximum engagement [21].

The Health Arcade project has designed to promote a change in geriatric patients’ routines during hospital stay by creating a favourable setting that will attract and motivate them for performing physical and cognitive activities to prevent iatrogenic nosocomial disability [22]. The main aim of this project is to validate the impact of a pilot-system of multidomain intervention (i.e., physical and cognitive training) using gamification technologies to improve patients’ functional abilities (Figure 1), while also encouraging personal motivation and internal locus of control, which have been shown to be predictive variables in health promotion [16,23,24].

## 2. Materials and Methods

### 2.1. Study Design and Setting

The Health Arcade utilized an uncontrolled, pre-post-test trial to determine the implementation of the prototype multidomain intervention based on physical and cognitive training using gamification technologies. This design was suitable for establishing the feasibility, appeal, and potential implementation of an innovative intervention prior to launching into a more costly and intensive randomized controlled trial design. The study will be implemented in the acute care for elderly (ACE) unit of the department of geriatrics in a tertiary public hospital (Hospital Complex of Navarre [CHN], Pamplona, Spain). This department is constituted by 35 beds allocated to the unit and a staff of 12 geriatricians. Admissions in the ACE unit proceed mainly from the accident and emergency department.

### 2.2. Study Participants and Eligibility Criteria

Older adults aged 75 or over admitted to the Department of Geriatrics of the CHN between September 2020 and January 2021. Inclusion and exclusion criteria are described in Table 1.

### 2.3. Participant-Selection and Consent Process

Participants will be identified during the geriatric assessment process at admission in the ACE unit. The geriatricians will conduct a screening interview to determine whether potentially eligible patients meet the inclusion criteria. Demographic characteristic (e.g., age, residence, and level of education, etc.) will be also included.

### 2.4. Ethics and Dissemination

The study followed the principles of the Declaration of Helsinki [25] and was approved by Hospital Complex of Navarre Clinical Research Ethics Committee on 6th November 2019 ID-PI_2019/96). All patients or their legal representatives provided written informed consent.

### 2.5. Interventions

The intervention will consist in a supervised training including cognitive and physical stimulation using the games of the Health Arcade prototype (developed by OUIPLAY sl., Dundee, UK). This pilot-system is made up of a selection of technologies, such as movement detection through Near-Field Communication Sensors, wireless communication systems, feedback systems (i.e., LEDs and screens), and game engine programmes for the use of virtual reality. The games will focus on different cognitive domains such as orientation, perception, attention span, working memory, language, and coordination. The intervention duration will be four to nine consecutive days. Additionally, the patients will receive encouragement for maintaining active during hospital stay and for reducing sedentary time. The details of the intervention are described in the Figure 2 and Table 2.

### 2.6. Outcomes Assessment

Feasibility will be considered in terms of the success of processes for recruiting and retaining participants and implementing the incentives program. The primary implementation-related outcome is the adherence to treatment (i.e., number of games and days completed during the intervention period), the reaction or response time and the number of success and failures in each game per day. These parameters are automatically recorded in real time by the Health Arcade prototype. We will consider as a measure of implementation success a score of at least 30 points per session. Secondary implementation-related outcomes are self-perceived grade of difficulty, satisfaction, enjoyment per game and session; perceived difficulties in handling the prototype hardware. These parameters are assessed by content validation questionnaire based on the Delphi Method.

Effectiveness was evaluated by comparing functional capacity and cognitive status outcomes at pre- and immediately post-intervention (with a minimum intervention duration of three consecutive days) or when completing a maximum of nine days of intervention. The functional capacity of participants will be evaluated by the Short Physical Performance Battery (SPPB), the total score ranging from 0 (worst) to 12 points (best) [26] which includes balance, gait, and rising from a chair test. The standing balance test consists of the ability to maintain the standing position for 10 s with three different foot position: parallel, semi-tandem, and tandem. Measurement of walking speed, the time needed to progress for 4 linear meters at the patient’s usual speed, assigning a different score according to the speed. Chair sit-to-stand evaluates the ability to stand from a chair 5 times in a row without using the arms. The SPPB test is considered a valid instrument for detecting frailty and predicting disability, institutionalization, and mortality [27,28].

The cognitive function will be screened by the Mini Mental State Examination (MMSE) test [29], Spanish version [30], which has been widely used to determine cognitive decline. The principle cognitive domains assessed are orientation to time (5 points), orientation to place (5 points), registration of three words (3 points), attention and calculation (5 points), recalling the three words (3 points), language (8 points), and visuospatial ability (1 point). The MMSE is scored out of 30 points, with a score of ≤23 points indicating likely cognitive impairment [31]. The cognitive function will be quantified by the Cambridge Revised Screening Test for the Assessment of Mental Disorders in Old Age (CAMDEX-R) [32], Spanish version [33]. The cognitive domains assessed are: orientation (10 points); language (30 points); memory (27 points); attention and calculation (9 points); praxis (12 point); abstract thinking (8 points); and perception (9 points). The CAMDEX-R is scored out of 105 points English version [32] and 107 points Spanish version [33].

In addition, the ADLs will be assessed using the Barthel Index, Spanish version; scale of 100 [functional independence] to 0 [severe functional dependence]) [34], an international, validated, and the most used tool to measure disability [35]. The mood status will be assessed by the 15-item Yesavage Geriatric Depression Scale; Spanish version; contain ten affirmative items and five negative, a score between 0–5 is normal and a score greater than 5 suggests depression) [36]. The quality of life will be assessed using the quality of life measured by the questionnaires EQ-5D-3L [37]. This instrument measures 5 dimensions of health status: mobility, self-care, usual activities, pain/discomfort, and anxiety/depression. Each dimension is rated according to the following levels: (a) no problems; (b) some problems; (c) extreme problems. Additionally, it contains a visual analogy scale (VAS) to quantify perceived health of 0 [worst health state imaginable] to 100 [best health state imaginable] EuroQol–5 Dimension; Spanish version of the EQ-5D32) [37,38]. Development of delirium will be assessed with the Confusion Assessment Method [39]. Changes in level of physical activity or mobility (step count, walking, and sedentary time per day, will be measured by accelerometer Actigraph^®^ (ActiGraph LLC, Pensacola, Florida, EEUU) [40] and NFC system Health Arcade). Lastly, changes in handgrip strength will be measured using a hand dynamometer (Takei 5401 Digital Dynamometer, Takei scientific instruments CO., LTD, Niigata, Japan) [41]. The maximum value will be recorded after two measurements in each hand. The measurement results are expressed in kilograms [42,43].

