### 2.7. Planned Statistical Analysis

We will not report significance tests as the feasibility uncontrolled pre-post design was not designed or powered to test hypotheses or to detect change. A convenience sample size of 40 participants will be selected in accordance with published guidance for feasibility and acceptability of the technology studies [44,45]. According to Hertzog [46], 10–40 subjects provide estimates precise enough to meet a variety of possible aim be considered for pilot studies. In an initial analysis, we will calculate the proportion of enrolled participants out of all eligible patients, participants who adhered to the intervention, and the dropout rates. Besides, a patient satisfaction survey for the use of Health Arcade will be collected and analyzed. Descriptive statistics will be used to summarise markers of feasibility and appeal.

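### Section 2.6 labels an uncontrolled pre-post comparison an evaluation of effectiveness, which the plan elsewhere says this feasibility study is not designed to provide

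*Protocol article*

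**What the plan says.** Two statements in the protocol article point towards an effect of the intervention.

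- Section 2.6, on the health outcomes: "Effectiveness was evaluated by comparing functional capacity and cognitive status outcomes at pre- and immediately post-intervention". The post measurement follows at least three and at most nine days of intervention. Physical function is measured by the SPPB; cognition is screened by the MMSE and quantified by the CAMDEX-R.
- Introduction: "The main aim of this project is to validate the impact of a pilot-system of multidomain intervention", with the purpose of improving patients' functional abilities.

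Three statements point the other way.

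- Section 2.1 describes the design as uncontrolled and gives its purpose: "This design was suitable for establishing the feasibility, appeal, and potential implementation of an innovative intervention prior to launching into a more costly" randomised trial.
- Section 2.7: "We will not report significance tests as the feasibility uncontrolled pre-post design was not designed or powered to test hypotheses or to detect change". The descriptive statistics named there are for feasibility and appeal.
- Section 4 says that the intended product is a protocol for a later randomised trial, and that this later trial will test effectiveness.

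The primary and secondary outcomes in section 2.6 are implementation measures.

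**The concern.** The two sets of statements cannot both govern the report. If section 2.6 and the Introduction govern, the report will contain a result presented as effectiveness. If sections 2.1, 2.7 and 4 govern, it should not.

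The label matters because the comparison cannot bear it. Every participant is being treated for an acute illness between the two measurements. Section 3 says that hospital care aims to resolve the acute phase and restore health, and also that hospitalisation can considerably impair function. Movement in either direction is therefore expected without the games. Repeating a cognitive test within days adds possible retest gain. This point is firmest for the CAMDEX-R, because section 2.6 describes the MMSE as a screen.

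At stake is what may be concluded. An improvement may be recovery or retest gain. A decline may still be smaller than it would have been without the intervention. The article does not say how these would be told apart, and it does not caution against a causal reading of the health outcomes.

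**Working it through.** **The plan's own figure.** The sample size of 40 is a convenience sample (section 2.7) with no alpha, power, effect size or SD behind it, so there is nothing to reproduce. It lies within the range of 10 to 40 that section 2.7 cites for pilot studies. The point does not depend on it.

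**What the comparison estimates.** For each outcome, the mean pre-post change is a sum:

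observed change = effect of the intervention + spontaneous change (recovery or hospital-associated decline) + retest gain (cognitive tests)

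The study observes only the left-hand side. A comparator would estimate the last two terms; section 2.1 provides none. The first term is therefore not identified, whatever the precision.

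**Illustration that precision is not the remedy.** None of the following inputs is in the documents except n=40. Assumptions: no intervention effect; a spontaneous mean improvement of d, in units of the SD of the change; normal approximation; two-sided 95% interval. The probability that the interval lies wholly above zero is

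P = Φ(d·√n − 1.96)

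| n | d (assumed) | d·√n − 1.96 | P |
|---|---|---|---|
| 40 | 0.2 | 1.26 − 1.96 = −0.70 | 0.24 |
| 40 | 0.5 | 3.16 − 1.96 = 1.20 | 0.89 |
| 40 | 0.8 | 5.06 − 1.96 = 3.10 | above 0.99 |
| 400 | 0.2 | 4.00 − 1.96 = 2.04 | 0.98 |

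By symmetry, a spontaneous decline of the same size gives the same probability of an interval wholly below zero. With d=0.2, going from 40 to 400 patients raises the chance of a misleading interval from 0.24 to 0.98. More patients estimate the mixture more precisely; they do not separate its parts.

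**What section 2.7 covers.** Its disclaimer concerns hypothesis tests and power. A mean change reported without a p-value, under the label of effectiveness, still carries a causal claim. The disclaimer therefore does not reach the attribution problem.

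**The case against.** The strongest reply is that the safeguards are already in the document. The primary and secondary outcomes are implementation measures, significance tests are ruled out, and effectiveness is assigned to a later trial. No sentence says outright that change will be credited to the games. On this view, one badly chosen word in section 2.6 is at most a slip.

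Much of this stands, and it limits the point. Several stronger readings that a reader might infer are not supported:

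- *That the abstract also plans an effectiveness evaluation.* It does not. It sets out a feasibility evaluation and lists health measures as other outcomes. Its sentence "The proposed intervention will increase accessibility of in-clinical geriatrics services, improve function, promote recovery of the health, and reduce economic costs" is a statement of expected benefit, not an objective or an analysis.
- *That section 2.7 says the study cannot detect change.* It says the study was not designed or powered to do so. Change may well be seen; the difficulty is in crediting it.
- *That every health outcome is labelled effectiveness.* The label covers physical function and cognition only. The Barthel Index, mood, EQ-5D and handgrip share the attribution problem but not the label.
- *That the mean change will size the later trial.* The article does not say so.
- *That the bias can be sized from the Introduction's 5% to 60% range for hospitalisation-acquired disability.* That range comes from cited literature and is not shown to apply to ambulatory patients with a Barthel Index of at least 60. Incident disability is not a defined outcome here.
- *That sampling error at n=40 measures the fault.* It measures precision, not recovery or retest bias.

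What the reply does not remove is the contradiction. Section 2.6 names an evaluation of effectiveness and the Introduction names impact as the main aim. This is stated text, not a detail left to an analysis plan.

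**Conclusion.** The point holds as a contradiction about what the study may conclude. Section 2.6 and the Introduction claim a purpose that sections 2.1, 2.7 and 4 withhold, and a single-arm comparison over three to nine days in acutely ill inpatients cannot serve that purpose.

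The direction of the bias is open, since both recovery and hospital-associated decline are plausible. Its size cannot be derived from the documents. The probabilities of 0.24 to above 0.99 at n=40 rest on assumed spontaneous changes of 0.2 to 0.8 SD; they show how the misreading arises and do not forecast it. That change would in fact be read as an intervention effect is an inference from the wording, softened by the absence of tests and the deferral to a randomised trial.

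The design, the primary outcomes and the descriptive analysis in section 2.7 are not in question here. What needs to change is the wording that fixes the conclusion.

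**What to change.** 1. In section 2.6, replace the opening of the effectiveness sentence with: *Within-patient change will be described, as exploratory, by comparing …*
2. Add to section 2.6 or 2.7: *Without a control group, change will not be attributed to the intervention, and no conclusion on effectiveness will be drawn.*
3. In the Introduction, reword the main aim as feasibility and acceptability, in line with section 2.1.
4. As a minor point, soften the abstract's sentence that the intervention will improve function and reduce costs, for example by stating these as hopes for the later trial. The article lists no economic outcome.

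The cost is wording only, with no new data, patients or assessments. Section 5 says that recruitment is open, so the change can be made before results are reported. The sponsor gives up an effectiveness statement that the design could not support. Adding a concurrent control would be a different study and is not proposed here.

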### 2.7. Planned Statistical Analysis

We will not report significance tests as the feasibility uncontrolled pre-post design was not designed or powered to test hypotheses or to detect change. A convenience sample size of 40 participants will be selected in accordance with published guidance for feasibility and acceptability of the technology studies [44,45]. According to Hertzog [46], 10–40 subjects provide estimates precise enough to meet a variety of possible aim be considered for pilot studies. In an initial analysis, we will calculate the proportion of enrolled participants out of all eligible patients, participants who adhered to the intervention, and the dropout rates. Besides, a patient satisfaction survey for the use of Health Arcade will be collected and analyzed. Descriptive statistics will be used to summarise markers of feasibility and appeal.

## 3. Expected Results/Discussion

Hospitalization is usually a sentinel event leading to disability, especially in older adults [1,2,3,4]. Although the hospitalization process gives the chance to solve the acute phases of the disease in order to restore the state of health, it can considerably affect the functional capacity of old patients. A growing number of studies are emerging focused on the iatrogenic effects and nosocomial disability developed during hospitalization, and currently these consequences are relevant in clinical practice. The iatrogenic nosocomial disability is mainly characterized by prolonged bed rest episodes, sedentary behaviours and little cognitive stimulation during the entire hospital stay. These low-mobility behaviours coupled with the impaired intrinsic capacity of older people precipitate many adverse effects, such as loss of independence of ADLs, cognitive impairment, reduced caloric intake, sarcopenia, higher risk of falls and social isolation; thus, increasing the likelihood of developing new disabilities and death [4,5,6,7,8,9].

Accordingly, our research team has successfully demonstrated that a multi-component intervention and early physical rehabilitation are a key element in preventing functional and cognitive impairment usually associated with hospitalization in older adults [47,48]. Although the exercise benefits on physical and cognitive function have been researched in hospitalized older medical patients, there is a gap in the research on the role that serious games may have in acute hospital settings among this population [21]. A gamification intervention which includes physical exercise and cognitive training can be an effective strategy to achieve changes in the sedentary behavior of the patients, and that is the reason for developing the validation of a pilot-system multidomain intervention for improving functional abilities during hospital stay. This intervention has been designed focused on the physical and cognitive abilities of the patients, the sociocultural context, and the preferences of older people; as well as the setting in which it is intended to be developed.

